## Abstract

**Background:**

Stroke is the leading cause of death worldwide. China faces a similar risk of stroke as developed countries because of considerable changes in lifestyle, such as overeating and smoking. Tai Chi is a traditional form of mind-body exercise that has been widely practiced in China for thousands of years. However, there are few studies on the effect of Tai Chi on the cardiopulmonary function of stroke patients in the recovery phase. Therefore, it is necessary to observe the effect of Tai Chi on the cardiorespiratory fitness of patients after stroke.

**Methods:**

This is a parallel-design, two-arm, analyst assessor-blinded, randomized controlled trial. A total of 226 stroke patients in the recovery phase will be recruited and assigned randomly to a control group or Tai Chi group at a 1:1 ratio. The patients in the Tai Chi group will perform the Tai Chi exercise. The patients in the control group will perform walking exercises. Patients in both groups will receive conventional treatments and healthy education. The primary outcomes will be VO_2peak_ and scores on the MOS item short form health survey (SF-36) scale. Secondary outcomes will include vital capacity (VC), ejection fractions (EF), and cardiac output (CO). The assessments of the tests will be performed at three time points (before exercise, at the end of exercise, and 6 weeks after exercise). Adverse events will be recorded faithfully during the study.

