### Outcomes {12}

#### Primary outcomes

VO_2Peak_: Peak oxygen uptake (VO_2Peak_) is a highly reproducible objective indicator of cardiopulmonary fitness by the cardiopulmonary exercise test (CPET), which reflects the maximum oxygen uptake achieved by the participant through maximum effort. Studies have shown that VO_2Peak_ is positively correlated with regional cerebral blood flow [25]. Measurement of VO_2Peak_ by CPET is generally recognized as the gold standard of cardiopulmonary capacity [26].SF-36: The SF-36 is a general health status parameter designed for population surveys or health assessments. It contains both physical health content (physical fitness, role-physical, body pain, general health) and mental health content (vitality, social fitness, role emotional, mental health). In this study, the SF-36 scale will be used to assess the effects of Tai Chi on the physical and mental health of stroke patients.

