### Sample size {14}

Sample size estimation in this trial is based on the expected improvement of VO_2Peak_ in 12 weeks of Tai Chi training in patients with heart failure [31]. After 12 weeks of intervention, the VO_2Peak_ of the aerobic exercise group and Tai Chi group was respectively 13.0 ± 4 ml/kg/min and 15.2±6 ml/kg/min. We set *α* = 0.05, *β* = 0.10. The sample size will be estimated according to the estimation formula:
$$ {n}_1={n}_2=2{\left[\frac{\left({t}_{2a}+{t}_{2\beta}\right)\;s}{\delta}\right]}^2 $$

It is estimated that a sample size of 94 participants per group will be required. Considering a 20% dropout and exit rate, we will recruit 226 participants, with 113 participants in each group.

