## Statistical methods

### Statistical methods for primary and secondary outcomes {20a}

Statistical analysis will be performed by statisticians who come from the third term using SPSS 20.0 software for Windows. Categorical variables will be expressed in terms of frequency or percentage, and continuous variables will be expressed in terms of mean and standard deviation. Primary and secondary outcome data collected after 13 weeks and 19 weeks will be compared with baseline data, respectively. For normally distributed variables, a *t* test will be used for statistical comparisons between groups. If it is nonnormal, then a nonparametric test is used. *P* values less than 0.05 will be considered statistically significant. To verify that the results are consistent, the primary outcome (change in VO_2Peak_ between baseline and 19 weeks) will be compared between the two groups using intention-to-treat (ITT) and per-protocol subject analysis (PPS). The Pearson correlation or Spearman correlation measures the correlation between two variables.

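### The protocol defines its primary outcome in conflicting ways and sets no success rule; if VO2peak or SF-36 may succeed alone, the false-positive chance is about 7–10% at one visit and 11–17% over two

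*Protocol article*

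**What the plan says.** Four parts of the protocol article bear on what counts as the primary result.

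- **Abstract, Methods.** "The primary outcomes will be VO_2peak_ and scores on the MOS item short form health survey (SF-36) scale". SF-36 enters in the plural, as scores.
- **Outcomes {12}, Primary outcomes.** VO2peak and SF-36 are listed side by side with no ranking. The SF-36 entry describes the instrument: "It contains both physical health content (physical fitness, role-physical, body pain, general health) and mental health content (vitality, social fitness, role emotional, mental health". That is eight domains, and no domain or summary score is named as the endpoint.
- **Statistical methods {20a}.** On timing: "Primary and secondary outcome data collected after 13 weeks and 19 weeks will be compared with baseline data, respectively". On the threshold, P "values less than 0.05 will be considered statistically significant". No alpha split, testing order or adjustment is given, and nothing says whether one outcome or both must succeed. The sentence on intention-to-treat and per-protocol analyses then reads: "the primary outcome (change in VO_2Peak_ between baseline and 19 weeks) will be compared between the two groups". That is one outcome at one visit.
- **Sample size {14}.** "We set *α* = 0.05, *β* = 0.10". The calculation uses VO2peak alone, with figures from heart-failure patients after 12 weeks of intervention.

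**The concern.** The abstract and Outcomes section give two primary outcomes. The statistical section gives two in one sentence and one in another. The visit differs as well: the sample size is built on VO2peak at the end of training, whereas the statistical section names 19 weeks, which is six weeks after training stops (13 + 6 = 19).

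A reader of the final report could therefore not tell from the protocol which result decides the trial. Under the two-outcome text and the flat threshold, one favourable test out of several could be presented as a positive primary result. SF-36 is the more vulnerable of the two: it is a health-status questionnaire answered by participants who, according to the blinding section {17a}, cannot be blinded. The stated objective concerns cardiopulmonary fitness, so a positive SF-36 result on its own would not answer it.

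**Working it through.** **Inputs from the protocol.** Two listed primary outcomes; two post-baseline visits (13 and 19 weeks); 0.05 for every test; for the sample size, 13.0 ± 4 versus 15.2 ± 6 ml/kg/min, beta 0.10, 94 per group, and 113 per group after dropout.

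**Assumptions, not in the protocol.** Tests are two-sided. The sentence on 13 and 19 weeks is read as a between-group test of change from baseline at each visit. Correlation between the two outcomes runs from 0 to 0.9 for two tests. For four tests it runs from 0 to 0.8 between outcomes and from 0.5 to 0.9 between visits.

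**Step 1: the plan's own figure.** The difference is 15.2 − 13.0 = 2.2. The pooled SD is √((16 + 36)/2) = √26 = 5.10. With one-sided alpha 0.05 and 90% power:

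n = 2 × (1.645 + 1.282)² × 26 / 2.2² ≈ 92.0, rounded up to 93 per group, close to the stated 94.

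With two-sided alpha 0.05 the same formula gives 113 evaluable per group, which does not match. The dropout step is 94 × 1.2 = 112.8, giving 113 per group and 226 in total. So the size is reproduced from VO2peak at one time point with a single 0.05. It makes no allowance for SF-36 or for a second visit.

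**Step 2: false-positive chance if any one test may succeed.** With no true effect on either outcome and k independent tests, the chance of at least one P < 0.05 is 1 − 0.95^k. Correlated tests were simulated as multivariate normal (1,000,000 draws per scenario).

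| Tests that may count as success | Independent | Assumed correlations |
|---|---|---|
| Two outcomes, one visit (k = 2) | 1 − 0.95² = 9.75% | 7.0% (r = 0.9) to 9.7% (r = 0) |
| Two outcomes, two visits (k = 4) | 1 − 0.95⁴ = 18.5% | 10.8% (0.8 between outcomes, 0.9 between visits) to 17.3% (0 and 0.5) |

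The two-test simulation also covers VO2peak alone at both visits: 9.0% at a correlation of 0.5 and 7.0% at 0.9. Dropping SF-36 without naming the visit would therefore not restore 5%.

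**Step 3: readings that hold 5% without adjustment.** If VO2peak at one visit is the only confirmatory test, the error is 5%. If both outcomes must be significant at one named visit, it is at most 5%. The intention-to-treat sentence points to the first reading, but the abstract and Outcomes section do not. The second reading appears nowhere.

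**The case against.** The best defence is that the statistical section does fix a single primary outcome, including the variable and the visit, and that the sample size and the only stated hypothesis fit VO2peak. On that reading the error is 5%. This part stands: a reader might infer that inflation is certain, and the text does not support that. But the phrase sits in a sentence about checking consistency between analysis sets. It neither demotes SF-36 nor sets a testing order, and it conflicts with two other sections.

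A second objection is that the choice of SF-36 score and the handling of multiplicity belong in an analysis plan that is not shown. As a complaint about silence, that would be fair. Here, however, the protocol itself states the two primary outcomes, the flat threshold and the competing single primary outcome. An analysis plan could settle these only by departing from one of the published statements. The protocol does not call its P values unadjusted; it simply mentions no adjustment.

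A third point concerns size. A reader might infer from the plural scores and the eight listed domains that nine tests per visit are planned, giving 1 − 0.95⁹ = 37% at one visit or 1 − 0.95¹⁸ = 60% over two. The documents do not support that. The Outcomes section describes what the scale contains and never says each domain is a confirmatory test. Independence is also implausible for domains of one instrument and for repeated visits. All that can be said is that the error would exceed the four-test range if domains were tested separately at both visits.

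**Conclusion.** The point holds as a contradiction in stated text with a conditional consequence. The protocol gives two incompatible accounts of what is primary, two candidate visits for VO2peak and no success rule. If either outcome may succeed alone, the false-positive chance is about 7–10% at one visit and about 11–17% over two, with 18.5% as the independence figure for four tests. These ranges rest on correlations the protocol does not give, but every scenario tried exceeded 5%. If VO2peak at 19 weeks is truly the only confirmatory test, there is no inflation, and it is the abstract and Outcomes section that need correcting. The text has to change on either account.

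**What to change.** Amend the abstract, Outcomes {12} and Statistical methods {20a} so that they agree:

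1. Make change in VO2peak at one visit the sole primary outcome. Choose the visit explicitly, because the sample size section points to the end of the 12-week intervention and the statistical section to 19 weeks. Settle this before any unblinded analysis.
2. Name one SF-36 summary score at the same visit as key secondary outcome, tested at the same 0.05 only if VO2peak is significant.
3. Report other SF-36 scores and the other visit with confidence intervals and no confirmatory claim.

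**Cost.** SF-36 can no longer carry a positive result alone. The trial started on 1 September 2020, so this changes an outcome in a running trial: it needs ethics approval through the amendment route in section {25} and a registry update. No patients are added and VO2peak loses no power.

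**Alternatives.** Requiring both outcomes to succeed at one named visit also controls the error, but the trial was not sized for SF-36. Splitting alpha to 0.025 each would keep both outcomes primary and lower VO2peak power at 94 per group (SD 5.10): from 90.5% to 84.1% on the one-sided convention that reproduces the sample size, or from 84.1% to 76.3% with two-sided tests. In the two-sided case, the drop from the planned 90% to 84.1% comes from sidedness and not from multiplicity.

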**Discussion:**

If the results are positive, this study will contribute to the establishment of further guided Tai Chi rehabilitation programs.

**Trial registration:**

Chinese Clinical Trial Registry ChiCTR2000034719. Registered on 16 July 2020.

## Administrative information

The order of the items has been modified to group similar items (see http://www.equator-network.org/reporting-guidelines/spirit-2013-statement-defining-standard-protocol-items-for-clinical-trials/).

## Introduction

### Background and rationale {6a}

Stroke is the leading cause of death worldwide [1]. Accordingly, stroke has become the top cause of death and disability in China [2], reducing the quality of life and increasing the economic burden on families and society.

After the occurrence of stroke, prolonged muscle weakness and dystonia [3] promote deformities of bones, joints, and ligaments [4], thereby causing balance and motor disorders. In addition, 44% to 74% of patients [5] still have varying degrees of cognitive impairment after a stroke, and 25% to 74% of patients suffered from psychological disorders such as depression [6]. Balance ability [7], motor ability, cognition [8], and mood [9] are positively correlated with cardiopulmonary fitness (CRF), which influences the survival rate after stroke [10]. Moreover, the time period after a stroke ranges from 10 days to 8 years, suggesting that the decline in cardiorespiratory fitness may persist for years after the stroke. CRF reflects [11] the ability of the circulatory and respiratory systems to supply oxygen to skeletal muscles during sustained, moderate-to-intense exercise physical activity. Poor cardiopulmonary fitness, due to low exercise for 1–3 years [12] after stroke, may be a secondary factor limiting rehabilitation [13]. Conversely, cardiopulmonary training and consequent improvements in cardiopulmonary fitness increase motor function, the frontal gray [14] (which is associated with emotion [15]) and hippocampal volumes [16] (which influence cognition [17]).

Traditionally, stroke rehabilitation has focused on primary neurological impairments, including muscle weakness and loss of coordination. The intensity of physical or occupational therapy activities is not sufficient to cause cardiopulmonary training effects [18]. Tai Chi is a traditional form of mind-body exercise that has been widely practiced in China for thousands of years. The fitness of this exercise is believed to facilitate the flow of qi through the body, thereby producing health benefits. There are various styles of Tai Chi, including Yang-style (24-form) and Sun-style (21-form) styles. Strong evidence has shown that Tai Chi improves or maintains balance ability in patients with Parkinson's disease [19]. In addition, Tai Chi has been shown to play a positive role in CRF. A study showed that Tai Chi significantly [20] reduced elderly obese people’s vital capacity and maximal oxygen uptake. Tai Chi improves [21] cardiopulmonary fitness parameters, including forced expiratory volume in 1 s (FEV1) and the 6-minute walk test (6MWT), in patients with chronic obstructive pulmonary disease (COPD). Moreover, Tai Chi has been widely practiced for stroke rehabilitation. Specifically, prior studies show that Tai Chi training may constitute a viable intervention not only to improve balance [22] and quality of life [23] in stroke survivors but also to support stroke prevention [24].

However, the effects of Tai Chi on specific stimulation actions for cardiopulmonary fitness have rarely been studied. Because 24-form Tai Chi requires higher strength, balance, and coordination of the upper and lower limbs, it is challenging for patients in the stroke recovery period to achieve psychosomatic exercise training effects. Therefore, six suitable movements were selected from the 24 forms of Tai Chi prepared by the General Administration of Sport of China in 1956. The “Six Forms of Tai Chi” are Commencing Form, Wave Hands Like Clouds, Repulse Monkey, Part the Wild Horse's Mane on Both Side, Hold the Lute, and Closing Form. We adapted six movements according to the theories of normal human anatomy, traditional Chinese medicine (TCM) meridians and collaterals, TCM Qigong, etc., to produce specific effects on cardiopulmonary fitness. To date, no studies have clarified the effect of “Six Forms of Tai Chi” training on the cardiopulmonary fitness of patients after stroke.

### Objectives {7}

Based on previous literature and training experience, our hypothesis is that “Six Forms of Tai Chi” training safely improves the cardiopulmonary fitness of stroke patients in the recovery phase.

### Trial design {8}

This study will be a multicenter, single blind (assessor and statistician), 19-week, randomized parallel control group trial. Patients will be allocated in a 1:1 ratio into the control group or Tai Chi group.

## Methods: Participants, interventions, and outcomes

### Study setting {9}

The patients will be recruited from the Xi Yuan Hospital, Beijing Da Xing District of Integrated Traditional Chinese and Western Medicine, Hebei Cang Zhou Hospital of Integrated Traditional Chinese and Western Medicine, Fujian University of Chinese Medicine, Henan Provincial People’s Hospital, The Third People’s Hospital of Zhengzhou, and Henan Provincial Hospital of TCM. Patients will be considered for inclusion if they meet the criteria defined below. The flow chart is shown in Fig. 1.

**Fig. 1 Fig1:**
[figure not shown]
Flow chart of the trial

### Eligibility criteria {10}

Inclusion criteria (at the outpatient clinic or inpatient)

Patients must meet the following criteria to be eligible for the study:
Key Points for the Diagnosis of Various Major Cerebrovascular Diseases in China 2019.2 weeks to 6 months after onset of stroke.Between 18 and 75 years of age.Berg balance ability scale > 40 points.Patients or their guardians must sign an informed consent form.

Exclusion criteria (at the outpatient clinic or inpatient)
Subarachnoid hemorrhage.Severe dysfunction or complications of liver and kidney.Peripheral facial paralysis, visual impairment, aphasia, and mental disorders that prevent the patient from completing the study.Recent acute coronary syndrome, including myocardial infarction or unstable angina (within 4 weeks).Patients with chronic obstructive pulmonary disease.Systolic blood pressure > 180 mmHg, diastolic blood pressure > 100 mmHg, and resting heart rate > 120 beats/min.Patients who participated in Tai Chi training within 3 months.MOCA scale ≤26 points.The 6-minute walking test was completed with a BORG score of less than 3 or greater than 7.

### Who will take informed consent? {26a}

Stroke patients in the recovery phase will be screened for eligibility to participate in this study based on the abovementioned criteria. After the patient has been assessed as eligible by the lead physician, he/she will receive initial study information. After at least 2 weeks of reflection, stroke patients in the recovery phase will be invited to meet with the research physician to discuss any remaining questions and sign the informed consent form.

### Additional consent provisions for collection and use of participant data and biological specimens {26b}

A total of 226 stroke patients will be asked to supply 10 ml of blood. These blood samples of patients will be drawn at baseline and at 13 and 19 months. Regardless of treatment allocation, patients will be made aware this part of the trial on the informed consent form.

## Interventions

### Explanation for the choice of comparators {6b}

According to the Physical Activity and Exercise Recommendations for Stroke Survivors, the control group will receive walking training with standard care and health education interventions.

### Intervention description {11a}

The participants in the Tai Chi group will undergo “Six Forms of Tai Chi” training in the garden of the hospital or campus gymnasium, with 60-minute sessions occurring five times a week for 3 months. Before formal training, Tai Chi teaching will be held for 1 week, including lessons on the knowledge of Tai Chi and the six movement standards of Tai Chi. Formal training will be conducted after all participants have similar assessment scores. According to the Physical Activity and Exercise Recommendations for Stroke Survivors, each session will include 40 min of Tai Chi training plus 10 minutes of warm-up and cool down, and the intensity will be 55–80% heart rate (HR) max. The six Tai Chi movements will be adapted by an expert panel from the Yang Short-form style that is based on the General Administration of Sport of China. The six movement main points are as shown in Table 1.

**Table 1 Tab1:** Chart of six movement main points

Number	Name	Main point	Breathing
Form 1	Commencing form	Raise palm	Inhale
		Down push both palms	Exhale
Form 2	Wave hands like clouds	Back pull on shoulders and elbows	Inhale
		Palm down	Exhale
Form 3	Repulse monkey	Turn and hold palm up	Inhale
		Return to palm and look forward	Exhale
Form 4	Part the wild horse’s mane on both side	Push palm in bow step	Inhale
		Exhale and settle palms	Exhale
Form 5	Hold the lute	Suction drives the shoulder up	Inhale
		The exhale pulls the shoulders back down	Exhale
Form 6	Closing form	Raised both arms	Inhale
		Down push both palms	Exhale

The six movements will be combined with abdominal breathing and will focus on cardiopulmonary fitness in stroke patients in the recovery phase. At the end of each training, the participants will be required to complete a “Tai Chi training log” to evaluate the training quality and compliance. Tai Chi training will be provided by Tai Chi coaches who achieved similar results in the qualification examination. All participants in the Tai Chi group will receive regular medical treatment and health education.

According to the Physical Activity and Exercise Recommendations for Stroke Survivors, the participants will conduct walking training. Before walking training, walking teaching will be held for 1 week. The training time, frequency and intensity were consistent with those of the Tai Chi group. Each session will include 40 min of walking exercise plus 10 min of warm-up and cool down. All participants in the control group will also receive regular medical treatment and health education as the Tai Chi group.

### Criteria for discontinuing or modifying allocated interventions {11b}

If the study meets any of the following criteria, the interventions will prematurely end. Patients can leave the study at any time for any reason if they wish to do so and will not face any consequences. Patient participation in this study can be ended by the investigator if the patient is uncooperative and/or does not attend study visits. During the study, patients with low adherence can affect the authenticity of the results. Interventions will be discontinued if there are abundant adverse events (AEs) or serious adverse events (SAEs).

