### Concealment mechanism {16b}

Allocation is not concealed and will be revealed to both the participants and the researcher upon randomization.

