## Assignment of interventions: blinding

### Who will be blinded {17a}

In this study, it will be impossible to blind the participants and Tai Chi coaches. To minimize bias, study personnel, such as researchers who perform relevant tests and outcome evaluators, will not have permission of a central stochastic system. Group A will be used to identify the control group, and group B will be used to identify the Tai Chi group, thus blinding the statisticians and outcome evaluators.

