### Methods in analysis to handle protocol non-adherence and any statistical methods to handle missing data {20c}

Missing data patterns will be analyzed by means of missing value analyses.

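### An investigator who knows the arm may end study participation for non-cooperation, so the promised intention-to-treat comparison can lose randomised patients for reasons that arise after randomisation

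*Protocol article*

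**What the plan says.** Four sections of the protocol article bear on this.

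- **Discontinuing or modifying interventions {11b}:** "Patient participation in this study can be ended by the investigator if the patient is uncooperative and/or does not attend study visits". A separate sentence follows: "During the study, patients with low adherence can affect the authenticity of the results". The section defines neither uncooperative behaviour nor low adherence, and does not say whether a patient whose participation has ended is still measured.
- **Concealment mechanism {16b}:** "Allocation is not concealed and will be revealed to both the participants and the researcher upon randomization". The blinding section {17a} covers those who run the tests, the outcome evaluators and the statisticians; its coding of the groups is described as "thus blinding the statisticians and outcome evaluators". The investigator who applies the {11b} rule is not among those named.
- **Statistical methods {20a}:** "the primary outcome (change in VO_2Peak_ between baseline and 19 weeks) will be compared between the two groups using intention-to-treat (ITT", with a per-protocol analysis beside it to verify that the results agree. For the between-group test: "For normally distributed variables, a *t* test will be used for statistical comparisons between groups", with a nonparametric test otherwise.
- **Retention {18b}:** all patients are to be reminded by telephone or WeChat to complete the assessments. The text does not say whether this includes patients whose participation was ended under {11b}.

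**The concern.** An ITT comparison needs outcomes from randomised patients whether or not they cooperated with their programme. The {11b} rule lets a person who knows the arm end a patient's place in the study on a judgement made after randomisation and without a stated threshold. If the 19-week measurement is then not taken, the change score does not exist for that patient.

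Two things are at stake. First, the protection that randomisation gives the primary comparison is weakened if removals, or the prognosis of those removed, differ by arm. Second, the ITT and per-protocol results are meant to check each other, and the check loses value as the two sets of patients become more alike. A later analysis plan can choose how to treat missing values, but it cannot recover measurements that the protocol allowed not to be taken.

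**Working it through.** **1. The plan's own figures.** Sample size section {14}: means 13.0 and 15.2, SDs 4 and 6, α = 0.05, β = 0.10.

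- Difference: 15.2 − 13.0 = 2.2 ml/kg/min.
- Pooled SD: √((4² + 6²)/2) = 5.10.
- The printed formula, iterated with t quantiles, gives 92.8 per group (93 rounded up) with a one-sided α. This is within one of the stated 94.
- Recruitment: 94 × 1.2 = 112.8, so 113 per group and 226 in all.
- A 20% loss leaves 113 × 0.8 = 90.4, about 90 per group. About 45 of the 226 (226 × 0.2 = 45.2) would lack a final value.

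The plan therefore expects a sizeable group without a 19-week value. The 20% covers dropout and exit together in both groups. It is not a forecast of removals by investigators.

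**2. How removal acts on the comparison.** In one arm, let r be the share removed and g the amount by which the removed patients would have scored below those retained. The full-arm mean is the retained mean minus r × g. The error in the between-arm difference, when only retained patients are measured, is

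bias = r(Tai Chi) × g(Tai Chi) − r(walking) × g(walking).

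**3. Illustrations.** The document gives neither r nor g, so every value of them below is an assumption. The 2.2 comes from a 12-week heart failure study and is carried to week 19 only for scale.

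| Removed, Tai Chi / walking | g, Tai Chi / walking | Bias (ml/kg/min) |
|---|---|---|
| 20% / 20% | 2.2 / 2.2 | 0.44 − 0.44 = 0 |
| 25% / 15% | 2.2 / 2.2 | 0.55 − 0.33 = 0.22 |
| 20% / none | 2.2 / – | 0.44 − 0 = 0.44 |
| 10% / 30% | 2.2 / 2.2 | 0.22 − 0.66 = −0.44 |

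In the third row the as-randomised difference is 0.8 × 2.2 = 1.76, while the retained patients show 2.2. The overstatement is 0.44, or 0.44/1.76 = 25% of the true value. The first row shows no bias and the fourth shows bias against Tai Chi.

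**4. The text, link by link.**

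- Stated: the investigator may end study participation; the researcher knows the arm; ITT is promised for change to 19 weeks.
- Inferred: that the researcher in {16b} includes the investigator in {11b}; that ending participation ends measurement; that a patient with no 19-week value is left out of the test.

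**The case against.** The strongest defence is that the text is ambiguous and not plainly wrong. The rule is permissive. It sits in a section about interventions, and {18b} reminds all patients to complete assessments. On that reading a removed patient might still be measured. This stands as far as it goes, but {18b} does not mention patients whose participation has ended, so the sections remain unreconciled.

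A second defence is that a patient who misses visits has no data whatever the rule says. This is largely right. The added loss falls on uncooperative patients who would still have come for testing, and perhaps on patients who missed week 13 but could have been measured at week 19.

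Several stronger readings are tempting, and the document does not support them:

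- *That {11b} removes patients for low adherence.* The sentence on low adherence carries no action. The stated grounds are non-cooperation and missed visits. A patient who trains poorly but attends visits is not clearly covered.
- *That the t tests necessarily discard removed patients, so that ITT becomes a completer analysis.* No section says so, and a t test can be run on imputed data.
- *That agreement of ITT and per-protocol results would show nothing.* This needs every non-adherer to be removed. The per-protocol set is not defined in the article and may exclude poor attenders who were measured and whom ITT would keep.
- *That the lack of a named imputation or modelling method is itself a fault.* Section {20c} says only "Missing data patterns will be analyzed by means of missing value analyses", but an article commonly leaves such detail to the full protocol or analysis plan.

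**Conclusion.** The point holds as an unresolved conflict between {11b} and {20a}, which {18b} does not settle. An unblinded investigator may end study participation on an undefined criterion, and the promised ITT comparison can lose randomised patients as a result. An unseen analysis plan would not cure this, because the loss occurs at data collection.

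The size of any bias is unknown. It is zero when removal and shortfall match across arms. It reaches 0.44 ml/kg/min in favour of Tai Chi when 20% of that arm alone are removed, gain none of the 2.2 and go unmeasured. It can also run the other way. A reader might infer from the 20% allowance that the plan itself implies a 25% overstatement. It does not: the allowance covers both arms and dropout and exit together, and the document gives no removal rate by arm. Nor does it show that adherence will differ between Tai Chi and walking, which are set at the same time, frequency and intensity.

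**What to change.** Reconcile {11b}, {18b} and {20a}:

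- In {11b}, separate stopping the training from leaving the study. State that non-cooperation or low adherence does not end outcome collection. When training itself should stop is a clinical matter on which this point takes no position.
- In {18b}, state that the primary outcomes are sought at weeks 13 and 19 from every randomised patient who has not withdrawn consent, including those who stopped training. The ITT promise in {20a} names only peak oxygen uptake, but SF-36 is also listed as primary.
- In {20a}, state that all randomised patients are analysed in the arm allocated, with the per-protocol analysis as supportive only. The choice of model and of missing-data method can be left to the analysis plan.

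The cost is an amendment to the wording, ethics review of it, and some effort to bring back patients who stopped training for visits already scheduled. The estimated effect may be smaller. The trial began on 1 September 2020, so patients already removed may be past their visits; their number and reasons by arm should then be reported.
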